### Trial profile

A CONSORT diagram will show trial participant flow. The number of screened patients, the patients who meet the inclusion criteria and trial subjects included in analyses will be reported together with reasons for exclusion of trial subjects.

### Primary outcome

The continuous FACT-P outcome score will be calculated using the official scoring guideline. As described in the scoring guideline missing items will be prorated by multiplying the sum of the subscale with the number of the items in the subscale, then divided by the number of items answered. This will be done if more than 50 % of the items are answered in the subscales and 80 % are answered in the total questionnaire. The change score of the total FACT-P at 12 weeks will be calculated by subtracting the total 12-week score from the respective trial participant's baseline score. Analysis of covariance will be used [32], group and ADT status will be set as factors, the response will be change in FACT-P and covariates will be age and baseline score. The results will be presented as least squares means (LSMEANS) differences between the two groups with 95 % confidence intervals and *p*-values.

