## Methods

### Trial design

The FCPC Trial is a randomised controlled parallel-group superiority trial with two parallel groups (community-based recreational football and usual care) that examines QoL after 12 weeks as the primary endpoint. Participants will be randomised (1:1) and the trial design is pragmatic [26].

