### Randomisation

*Sequence generation*, the allocation of participants, will be done using a computer-generated list of random numbers. The allocation will be stratified by center and by androgen deprivation status (yes/no) with a 1:1 allocation using random block sizes. A statistician not involved in the trial uploaded all the allocation sequences in the trial management system. The eligibility

[figure not shown]

[figure not shown]

**Fig. 3** Assumed causal pathways

of participants will be assessed by either investigators or project nurses at each center. The randomisation will be performed centrally by researchers at the University Hospitals Centre for Health Research, Copenhagen University Hospital, Rigshospitalet.

*Allocation concealment* will be implemented, as the allocation sequence will be hidden from the researchers and, using web-based trial management, no one other than the statistician who uploads the random number lists have access to the lists.

**Table 3** Outcomes with specified measurement variable, analysis metric, method of aggregation and time point

| Concept                         | Specific measurement variable                                       | Patient- level analysis metric | Method of aggregation | Time point(s)       |
|---------------------------------|---------------------------------------------------------------------|--------------------------------|-----------------------|---------------------|
| Primary outcome                 |                                                                     |                                |                       |                     |
| Quality of life                 | Functional Assessment of Cancer Therapy - Prostate Questionnaire    | Change from baseline           | Mean                  | 12 week             |
| Secondary outcomes              |                                                                     |                                |                       |                     |
| Quality of life                 | Functional Assessment of Cancer Therapy - Prostate Questionnaire    | Change from baseline           | Mean                  | 6 month             |
| Muscle mass                     | Whole-body lean body mass                                           | Change from baseline           | Mean                  | 6 month             |

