### Secondary outcomes including safety outcomes

Changes from baseline to six months for LBM, BMD, BMC and total body fat mass will be analysed in the same manner as the primary outcome.

QoL, functional well-being and physical activity (based on metabolic equivalent of task values derived from IPAQ) measured at baseline, 12 weeks and six months will be analysed using a mixed model for repeated

measurements. Changes from baseline to 12 weeks or six months will be treated as the response. The model will include fixed effects of factors: group, ADT, sampling time and their interactions, and the analysis will be adjusted for age and baseline value. The correlation between measurements on the same participant will be modelled using a random effect of participant.

Safety outcomes will be listed for each group and the number of falls that resulted in seeking medical assessment and fractures will be compared across groups using Fisher's exact test.

Subgroup analyses will be reported for the patients treated with ADT, which means that results will be given for both the overall treatment effect and for the subgroup obtained by stratifying according to ADT. To verify the credibility of our subgroup analyses, we will apply the criteria proposed by Sun and colleagues [33], i.e. the subgroup variable is a baseline characteristic, a stratification factor, specified a priori and includes only a small number of analyses.

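### Randomisation is stratified by center and ADT status, but the regression models carry only ADT; if center is prognostic, the standard errors are conservative and precision is forgone

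*Protocol*

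**What the plan says.** Under Randomisation, the protocol states: "The allocation will be stratified by center and by androgen deprivation status (yes/no) with a 1:1 allocation using random block sizes". There are thus two stratification factors.

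Under Primary outcome, the ANCOVA for the 12-week FACT-P change is given term by term: "group and ADT status will be set as factors, the response will be change in FACT-P and covariates will be age and baseline score". ADT is there; center is not.

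Under Secondary outcomes including safety outcomes, the six-month changes in lean mass, fat mass, bone density and bone content "will be analysed in the same manner as the primary outcome", so they inherit the same terms. The repeated-measures model for quality of life, functional well-being and physical activity has as its fixed factors "group, ADT, sampling time and their interactions, and the analysis will be adjusted for age and baseline value". Its only random term is for the participant: "The correlation between measurements on the same participant will be modelled using a random effect of participant".

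Center therefore appears in none of these models, as a fixed or a random effect, and no reason is given. The terms are listed explicitly, so this is a stated choice and not a detail deferred to an SAP.

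**The concern.** The analysis follows one half of the stratification and drops the other. Stratified blocking makes the arms nearly equal in size within each center, so differences between centers largely cancel from the treatment comparison. A model without center does not know this: it counts between-center variation as residual noise and attaches that noise to the treatment effect. Where center is prognostic, the confidence interval is wider than the true sampling variation warrants, the test rejects less often than 5% under the null, and precision that the design has already secured is not used.

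The sample size leaves little slack: the stated inputs need 99 to 100 per group, 100 are planned, and recruitment ends on 1 May 2017 even if the target has not been reached. Precision that costs no extra participants is worth having.

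**Working it through.** **Inputs from the protocol (Sample size and power considerations):** difference 6 points, SD 15, two-sided 5%, power 80%, 100 per group.

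**Inputs that are assumed:** the share r of residual variance due to center, after ADT, age and baseline. The protocol gives neither this share nor the number of centers, so a range from 0 to 20% is shown.

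**Step 1: reproduce the plan's figure.** n per group = 2 × 15² × (1.960 + 0.842)² / 6² ≈ 98.1, so 99 by the normal approximation. The noncentral-t calculation gives 100 per group with power 80.4%. The stated 100 reproduces.

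**Step 2: formula for the effect of omitting center.** Assume exact balance within centers and a total residual SD of 15.

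- SE reported without center: 15 × √(2/100) = 2.121.
- True SE: 2.121 × √(1 − r).
- Excess width: 1/√(1 − r) − 1.
- True type I error without center: 2 × [1 − Φ(1.96/√(1 − r))].
- Power without center: Φ[(6 − 1.96 × 2.121)/true SE].
- Power with center: Φ[6/true SE − 1.96].

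| r (assumed) | True SE | Reported SE too wide by | True alpha | Power without center | Power with center | Gain (points) |
|---|---|---|---|---|---|---|
| 0 | 2.121 | 0% | 5.0% | 80.7% | 80.7% | 0 |
| 2% | 2.100 | 1.0% | 4.8% | 81.0% | 81.5% | 0.5 |
| 5% | 2.068 | 2.6% | 4.4% | 81.4% | 82.7% | 1.3 |
| 10% | 2.012 | 5.4% | 3.9% | 82.0% | 84.7% | 2.7 |
| 20% | 1.897 | 11.8% | 2.8% | 83.4% | 88.5% | 5.1 |

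Power without center rises slightly with r because the total SD is held at 15 while the true sampling error shrinks.

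**Step 3: check by simulation.** N = 200, five centers, 40% on ADT, and random blocks of 2, 4 or 6 within center × ADT (all assumed); 6,000 runs per setting under the null.

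| r | Mean reported SE | Empirical SE | Too wide by | Rejection without center | Rejection with center |
|---|---|---|---|---|---|
| 0 | 2.118 | 2.125 | about 0% | 0.050 | 0.049 |
| 2% | 2.115 | 2.097 | 0.9% | 0.046 | 0.047 |
| 5% | 2.108 | 2.053 | 2.7% | 0.046 | 0.050 |
| 10% | 2.098 | 2.030 | 3.3% | 0.045 | 0.052 |
| 20% | 2.074 | 1.898 | 9.3% | 0.032 | 0.049 |

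The Monte Carlo error of an empirical SE from 6,000 runs is about 1/√12,000 = 0.9%, so the rows at 2% and 5% agree with the formula. At 10% and 20% the simulated excess is smaller: with few centers the sample contains less than the full between-center variance, and incomplete blocks leave some imbalance. The formula is best read as an approximate upper figure.

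**Step 4: an effect that differs between centers.** With center variance and center-by-treatment variance each set at 5% of the total, the reported SE without center is 2.131 against an empirical 2.569, and rejection is 0.099. Adding a center main effect leaves rejection at 0.110. Effects were redrawn in every run here, so this concerns inference to a wider population of centers and not the average effect in the participating ones.

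**The case against.** The strongest reply is that nothing in the protocol shows center to be prognostic for the change score. FACT-P is self-reported through the same web system and e-mail routine in both groups, and the model already adjusts for baseline, age and ADT. If center adds nothing after that, the standard error is right as planned. This stands: a reader might infer from the mismatch that the planned standard errors are wrong, and the documents do not support that without the condition.

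A reader might also infer that the trial loses its planned power or breaches its error rate. Neither follows. In every scenario above, power without center is at or above 80%, so what is forgone is a gain and not planned power. A conservative test also respects the 5% ceiling under Statistical methods.

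For the DXA outcomes, scanners that differ between centers may seem to make matters worse. The outcomes are within-person changes, so a constant offset largely cancels if each man is rescanned on the same machine, and the protocol does not say that scanners differ.

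Finally, football is delivered by local club coaches, and Step 4 shows that a varying effect could make the standard error too narrow for a wider population of centers. That too is an assumed scenario, but it means the direction is not certain for every estimand.

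What the reply does not answer is the mismatch itself: one stratification factor is modelled and the other is not, without explanation.

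**Conclusion.** The point holds in conditional form. Of the two stratification factors, only ADT is in the primary ANCOVA, the DXA ANCOVAs and the repeated-measures model, alongside age and baseline value. If center predicts change after those adjustments, inference is conservative and available precision goes unused. For assumed shares of 0 to 20%, the reported SE is 0 to about 12% too wide by formula (about 9% at the top of the range in simulation), true alpha lies between 5.0 and 2.8%, and adding center gains 0 to about 5 points of power.

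Confidence is high on the omission and only moderate on its size, because the center share, the number of centers and the ADT mix are all assumptions. The figures are for the primary ANCOVA; the same mechanism applies to the other models, but was not quantified for them. The treatment estimate is unbiased, the sample size of 200 is unaffected, and the omission alone does not inflate type I error. This is a modest inefficiency that should be corrected, not a threat to validity.

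**What to change.** Add center to the primary ANCOVA, the DXA ANCOVAs and the repeated-measures model, as a fixed effect. If some centers are very small, use a random intercept for center, or pool small centers. The choice and any pooling rule should be written down before unblinding, and preferably before the coded groups A and B are compared. If the sponsor prefers to leave center out, the protocol should say why.

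The cost is a change of wording and a few degrees of freedom: with 200 participants the primary model has 200 − 5 = 195 residual degrees of freedom, and five centers (assumed) would take 4 more, leaving 191. No new data are needed, since center is already recorded for stratification.

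A center main effect does not address a football effect that differs between centers; that is a separate question.

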### Secondary outcomes including safety outcomes

Changes from baseline to six months for LBM, BMD, BMC and total body fat mass will be analysed in the same manner as the primary outcome.

QoL, functional well-being and physical activity (based on metabolic equivalent of task values derived from IPAQ) measured at baseline, 12 weeks and six months will be analysed using a mixed model for repeated

measurements. Changes from baseline to 12 weeks or six months will be treated as the response. The model will include fixed effects of factors: group, ADT, sampling time and their interactions, and the analysis will be adjusted for age and baseline value. The correlation between measurements on the same participant will be modelled using a random effect of participant.

Safety outcomes will be listed for each group and the number of falls that resulted in seeking medical assessment and fractures will be compared across groups using Fisher's exact test.

Subgroup analyses will be reported for the patients treated with ADT, which means that results will be given for both the overall treatment effect and for the subgroup obtained by stratifying according to ADT. To verify the credibility of our subgroup analyses, we will apply the criteria proposed by Sun and colleagues [33], i.e. the subgroup variable is a baseline characteristic, a stratification factor, specified a priori and includes only a small number of analyses.

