### Sample size and power considerations

The sample size calculation is based on the detection of a minimal clinical important difference between groups on six points on the FACT-P questionnaire [28] at 12 weeks with a standard deviation of 15 FACT\_P points. A two-sided significance level of 5 % and power of 80 % were chosen; The standard deviation is based on a previous exercise trial [30] but increased slightly as FCPC participants will be more heterogeneous than the participants in that trial. Consequently, 100 participants will be needed in each group, i.e. 200 participants in total, in order to detect a statistically significant difference between groups. No interim analysis will be performed. However, if the

anticipated sample size has not been enrolled by 1 May 2017, recruitment will end and final analyses will be performed with the number of patients recruited at that point.

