## Statistical methods

### Plan for statistical analyses

The primary statistical analysis targets the effect on PCA specific QoL of a treatment policy offering community-based football to men with PCA. In particular, patients will be analysed in the treatment group to which they were randomly allocated according to the intention-to-

treat principle. The appropriate method for addressing this effect will depend on the assumptions made about missing data (dropouts). Our main analysis is valid under the missing at random assumption but we will also present sensitivity analyses robust to non-ignorable patterns among patients with incomplete data.

Per protocol analyses will be performed to estimate the de jure effect of the treatment for compliant patients. The per protocol population will be defined as intervention group participants who attended the football intervention at least 12 times in the first 12 weeks and 24 times in the six-month intervention period.

Significance tests will be two-sided with a maximal type I error risk of 5 %. To address the problem of multiple comparisons for secondary analyses when several outcomes are tested or multiple constructs are extracted from the same statistical model, p-values will be adjusted using the step-down Bonferroni method of Holm [31] or appropriate modern alternatives.

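### The random participant effect, with its usual constant residual variance, assumes equal spread at 12 weeks and six months; separate variances by visit would protect five secondary tests for one extra parameter

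*Protocol*

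**What the plan says.** Under Secondary outcomes including safety outcomes, the protocol puts QoL, functional well-being and IPAQ-based physical activity into a mixed model for repeated measurements. Each man contributes two responses: "Changes from baseline to 12 weeks or six months will be treated as the response". The fixed effects are group, ADT, sampling time and their interactions, adjusted for age and baseline value. The covariance is described in one sentence: "The correlation between measurements on the same participant will be modelled using a random effect of participant". The protocol does not say whether the residual variance is constant or may differ by visit.

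Table 3 asks this model for five secondary results tied to a visit: QoL at six months, and physical activity and functional well-being each at 12 weeks and at six months. The primary outcome (12-week FACT-P change) and the six-month DXA outcomes are analysed by separate ANCOVAs.

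**The concern.** A random intercept per participant plus one residual variance is compound symmetry. With two post-baseline visits, the main restriction is that the change scores have the same variance at 12 weeks and at six months. The spread of change scores need not stay constant; it can grow if correlation with baseline weakens over time. The model would then pool two different variances and attach the same standard error to both contrasts.

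At stake are the confidence intervals and p-values of the five results above: too optimistic at the more variable visit, with lost power at the other. The Holm adjustment planned for secondary outcomes would start from those p-values.

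**Working it through.** **Inputs from the protocol** (Sample size and power considerations): "A two-sided significance level of 5 % and power of 80 % were chosen"; a "minimal clinical important difference between groups on six points"; "with a standard deviation of 15" FACT-P points, given for 12 weeks only; "100 participants will be needed in each group, i.e. 200 participants in total". Allocation is 1:1.

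**Assumed, because the protocol does not give them:** the ratio r of the six-month to the 12-week SD (baseline-adjusted change), a within-participant correlation of 0.6, and 0% or 15% missing at six months.

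**1. The plan's own figure.** n per group = 2 × (1.960 + 0.842)² × 15² / 6² = 98.1, so 99 by the normal approximation. The noncentral t gives 99.08, so 100. The stated 100 per group is reproduced, with power of about 80%. It concerns the primary ANCOVA and does not depend on the repeated-measures model.

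**2. Effect of pooling, complete data.** Let s₁ and s₂ be the SDs at 12 weeks and six months, with s₂ = r × s₁. The common-variance model uses s_p = √((s₁² + s₂²)/2) at both visits. Then

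- model SE / true SE at a visit = s_p / s_visit;
- actual type I error at nominal 5% = 2 × [1 − Φ(1.96 × s_p / s_visit)].

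Example, r = 1.2 with SDs of 15 and 18: s_p = √((225 + 324)/2) = 16.57. With 100 per group the true SEs are 15 × √0.02 = 2.12 and 18 × √0.02 = 2.55. The model reports 16.57 × √0.02 = 2.34 at both visits.

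| r | SE ratio, 12 weeks | SE ratio, six months | Type I error, 12 weeks | Type I error, six months |
|---|---|---|---|---|
| 1.0 | 1.000 | 1.000 | 5.0% | 5.0% |
| 1.1 | 1.051 | 0.956 | 3.9% | 6.1% |
| 1.2 | 1.105 | 0.920 | 3.0% | 7.1% |
| 1.25 | 1.132 | 0.906 | 2.7% | 7.6% |
| 1.5 | 1.275 | 0.850 | 1.2% | 9.6% |

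If six months is the less variable visit, the columns swap: at r = 0.8 (= 1/1.25) the errors are 7.6% at 12 weeks and 2.7% at six months.

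**3. Simulation check.** REML random-intercept fit, 100 per group, no true effect, 6,000 trials per setting (Monte Carlo error about 0.3 percentage points near 5%). The last column is the group effect averaged over visits.

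| r | Missing at six months | 12 weeks | Six months | Averaged |
|---|---|---|---|---|
| 1.0 | 0% | 4.7% | 4.9% | 4.9% |
| 1.1 | 0% | 4.1% | 6.3% | 5.2% |
| 1.2 | 0% | 3.1% | 7.0% | 4.6% |
| 1.5 | 0% | 1.0% | 9.0% | 4.8% |
| 1.2 | 15% | 3.7% | 7.8% | 5.8% |
| 1.5 | 15% | 1.5% | 10.1% | 6.2% |

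Missingness was generated completely at random, so these runs say nothing about bias from selective dropout.

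**4. At a stricter threshold.** Table 3 lists 12 non-safety secondary tests when each time point is counted. If they form one Holm family (an assumption), the first threshold is 0.05/12 = 0.0042, that is z = 2.865. At r = 1.2 the actual rate at six months is 2 × [1 − Φ(2.865 × 0.920)] = 0.0084, about twice nominal. At 12 weeks it is 0.0016.

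**The case against.** The strongest reply is that the sentence in question speaks of correlation and is silent on residual variance. A random participant effect can be combined with visit-specific residual variances, and an SAP, which is not at hand, may say so. This stands. A reader might infer that the protocol forces one variance on both visits; it does so only under the usual default.

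Second, nothing in the protocol shows unequal spread. Its one SD is for 12 weeks, and every ratio above is assumed. Modest ratios may be the realistic ones. If the score SD were the same at all visits and the correlation with baseline fell from 0.6 to 0.5, the baseline-adjusted SD ratio would be √(1 − 0.25)/√(1 − 0.36) = 1.08, giving about 5.9% at six months and 4.1% at 12 weeks. This stands too. A reader might conclude that the secondary p-values are wrong; the documents support only that they could be miscalibrated, by an amount that depends on the SD ratio.

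Third, with complete data the visit-averaged contrast keeps its level. That is true, but Table 3 lists visit-specific results, so it does not answer the point.

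Fourth, a reader might extend the point to biased six-month means under dropout, citing "Our main analysis is valid under the missing at random assumption". That sentence follows the description of the primary analysis, which is the separate ANCOVA, and no such bias has been quantified here. The point does not rest on it.

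What remains is that the protocol does name a covariance model, that its default reading carries an equal-variance assumption, and that the assumption buys nothing with two visits and about 200 men.

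**Conclusion.** The point holds as a minor improvement to secondary analyses. Read with constant residual variance, the stated model assumes equal spread at both visits. The resulting type I error at the more variable visit is about one percentage point too high at an SD ratio of 1.1, two points at 1.2 and two and a half at 1.25, with a conservative error at the other visit. These sizes rest on assumed ratios and complete data. They apply to five secondary tests and leave the primary result, the 100 per group and the DXA outcomes untouched. The stronger claim, that these analyses are invalid as planned, is not supported.

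**What to change.** In Secondary outcomes including safety outcomes, replace the random participant effect with an unstructured 2x2 within-participant covariance, or keep the random effect and add visit-specific residual variances. Fit by REML with Kenward-Roger degrees of freedom, and report the group contrasts at 12 weeks and at six months. If separate variances are already intended, saying so is enough.

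The cost is one sentence and one extra variance parameter. With about 200 men and two visits, convergence and degrees of freedom should not be a difficulty. Data collection and sample size do not change. In the example above, the SEs would become 2.12 and 2.55 in place of 2.34 at both visits.
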